### Participants

2.2

This study will include 15 patients with MCS, 15 patients with UWS, and 15 healthy subjects sourced from various hospitals. Before enrollment, each DoC patient will undergo five assessments using the Coma Recovery Scale-Revised (CRS-R) over a 10-day period conducted by assessment experts. The best result from the five assessments will be considered as the patient’s current level of consciousness, and assessment experts will assess if the patient meets the inclusion criteria during the evaluation process.

The criteria for inclusion and exclusion are outlined in Table 1.

**Table 1 tab1:** Inclusion and exclusion criteria.

Inclusion criteria	Exclusion criteria
Diagnosed in DoC with 5 times CRS-R assessments;	Active seizures or a history of mental illness;
Disease onset more than 28 day;	Metal implants in the skull;
Intact skin and anatomical structure;	Lack of motor evoked potential from right first dorsal interosseous muscle;
Right-handed as per Edinburgh Handedness Inventory;	Unstable vital signs;
Stable central nervous system drug therapy for 1 week before enrollment.	Use sedatives, sodium or calcium channel blockers.

DoC, disorders of consciousness; CRS-R, Coma Recovery Scale-Revised.

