### Procedures

2.4

The study process will begin as early as 28 days after the patient’s injury, and the entire experimental process will be finished within 10 days. After informing the patient’s legal representative about the experimental content and potential adverse reactions, written informed consent will be obtained from them. They will be advised that they can choose to exit the study at any time without the requirement for providing a reason. After informing the healthy subjects of the experimental content and potential adverse reactions, they will sign the informed consent form.

Before the trial, DoC patients will have the option to undergo a functional magnetic resonance imaging (fMRI) scan, and they can choose to decline. Over a period of 10 days, five CRS-R assessments, and an fMRI scan will be completed. The study protocol is a repeated-measures crossover design. According to different tDCS priming protocols (anode, cathode, sham), the trial will be divided into three distinct sessions. Each session will involve 10 min of tDCS priming followed by 192 s of TMS test, with both transcranial stimulations specifically targeted toward the left M1. We will measure the motor evoked potential (MEP) amplitude at four time points: baseline (PRE), after tDCS (INTER), and at 5 and 15 min following TMS (POST-1, POST-2). CRS-R data will be collected at baseline (PRE) and 20 min after TMS (POST-3). Upon enrollment, participants will receive a serial number based on their order of enrollment, with each serial number corresponding to a randomly generated session order. Subjects will then undergo three sessions following the designated session order, with a two-day washout period between each session. The entire trial will be completed in 5 days. Patient prognostic data will be gathered at 3, 6, and 12 months after the conclusion of the study. Figure 1 provides a detailed illustration of the study flow.

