### Statistical analysis

2.11

A single transcranial stimulation typically leads to limited behavioral improvement but increases cortical excitability due to its immediate effects (36). Therefore, the primary focus of this study will be to analyze the trend of MEP changes over time in different priming types, comparing healthy individuals with DoC patients. At the individual level, the cathodal tDCS group will be compared with the sham group. The primary outcome of this study will be MEP, a measure used to assess neurophysiological changes. Since the baseline MEP in each session will be influenced by various factors such as the individual’s daily state, MEP data from different sessions will lack comparability. Therefore, all MEP data will be normalized in this study (normalized MEP = MEP/MEP baseline). The normalized MEP data will be subjected to an analysis of variance (ANOVA) to explore the retention of homeostatic plasticity in DoC patients and to determine whether the combination of cathodal tDCS and iTBS is superior to iTBS alone.

While a single stimulus may not directly lead to a change in behavior, this study will conduct a CRS-R assessment (specific item) before and after each session to ensure that any potential improvements are not overlooked. Homeostatic plasticity, as a fundamental characteristic of synapses, can impact a range of synaptic activities and may even influence levels of consciousness and prognosis. Therefore, the CRS-R score, which assesses the level of consciousness, will be considered as a secondary outcome of this study.

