Patients will be categorized into subgroups based on consciousness levels and prognosis. For consciousness levels, patients will be classified into the MCS or UWS group based on the best result from five baseline CRS-R assessments, To classify a CRS-R record as reflecting MCS, the participant must achieve at least one of the following criteria: a score of 1 on the communication subscale (intentional but non-functional yes/no communication), a score of 3 or higher on the auditory subscale (command-following), a score of 2 or higher on the visual subscale (visual fixation or better), a score of 3 or higher on the motor subscale (localization to noxious stimulation or better), or a score of 3 on the oromotor/verbal subscale (intelligible verbalization). If none of these criteria are met, the CRS-R record will be classified as reflecting UWS (37). For prognosis, patients will be evaluated at 3, 6, and 12 months, with those showing an increase of over 11 Rasch units (approximately 4–6 CRS-R points) (38) classified as the good prognosis group, while others will be placed in the poor prognosis group. A preserved homeostatic plasticity response is defined as a significant modulation of MEP amplitude following the priming-test protocol, consistent with the sliding threshold theory of synaptic plasticity. Its preservation was further compared between the MCS and UWS groups, as well as between the good and poor prognosis groups.

In this study, statistical analysis will be conducted using IBM SPSS Statistics 26 software. The collected data will first undergo normal distribution testing via Kolmogorov–Smirnov tests. If the data meets the criteria for a normal distribution, a three-way repeated measures ANOVA will then be carried out. However, if the data does not adhere to a normal distribution, Friedman’s ANOVA will be utilized instead. Following a significant outcome from the ANOVA, two-way ANOVAs will be conducted within each group to explore temporal changes in mean MEP amplitude. Additionally, Pearson correlation will be used to examine the relationship between homeostatic plasticity retention, consciousness, and prognosis. A significance level of *p* < 0.05 will be employed for determining statistical significance.

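### The non-normality fallback, Friedman's ANOVA, has no group factor and no interaction, so the healthy-versus-DoC comparison would have no valid named test

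*Protocol article*

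**What the plan says.** All references are to the Protocol article.

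- **Question.** Under Statistical analysis (2.11), the primary focus is to "analyze the trend of MEP changes over time in different priming types, comparing healthy individuals with DoC patients". The primary outcome is MEP, expressed as a ratio to the baseline of the same session because sessions are not otherwise considered comparable.
- **Design.** Participants (2.2): "This study will include 15 patients with MCS, 15 patients with UWS, and 15 healthy subjects". Procedures (2.4): "According to different tDCS priming protocols (anode, cathode, sham), the trial will be divided into three distinct sessions", with MEP measured at PRE, INTER, POST-1 and POST-2.
- **Decision rule.** Statistical analysis (2.11): "The collected data will first undergo normal distribution testing via Kolmogorov–Smirnov tests". If normality is accepted, a three-way repeated measures ANOVA follows. Otherwise, "if the data does not adhere to a normal distribution, Friedman’s ANOVA will be utilized instead".
- **What else is named.** After a significant ANOVA, two-way ANOVAs are run inside each group. Preservation of homeostatic plasticity is also to be compared between MCS and UWS and between prognosis groups, with no test named, and a Pearson correlation relates preservation to consciousness and prognosis.

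**The concern.** The two branches of the rule do not test the same thing. The first has group as a between-subject factor, with priming and time crossed within subject. The second is a one-factor, within-subject rank test. The word that links them makes the second a replacement for the first, not a supplement to it.

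If the K-S test rejects, the trial keeps its data but loses the only named test that sets healthy controls against DoC patients and asks whether the priming response differs between them. Impairment of homeostatic plasticity in DoC relative to health is the first part of the first hypothesis in the Introduction. Whether it gets a valid test would then hang on a preliminary test of the data.

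**Working it through.** **1. What each branch can test.**

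| Effect | Three-way ANOVA | Friedman |
|---|---|---|
| Group (healthy, MCS, UWS) | yes | no |
| Group × priming, group × time, group × priming × time | yes | no |
| Priming at one fixed time, within subject | yes | yes |
| Priming × time, within subject | yes | no (one factor only) |

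**2. Why group drops out.** For n participants and k conditions, with R_j the sum over participants of the within-participant ranks for condition j,

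χ²_F = 12 / [n k (k+1)] × Σ R_j² − 3 n (k+1).

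Only within-participant ranks enter. Adding a constant to every value of a participant leaves the ranks unchanged, and moving participants between groups leaves each R_j unchanged. The statistic is therefore the same whatever the group labels. Numerical check: relabelling participants across groups, or adding 0, 5 and 10 to the three groups, gave χ²_F = 5.1437, p = 0.742 each time. This needs no assumption about the data.

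**3. What this does to power.** Simulation of 3 groups × 15 with three priming conditions, 4,000 runs. Assumptions: lognormal ratios with participant SD 0.3 and error SD 0.3 on the log scale, and group shifts of +0.4, 0, −0.4 in the pure group scenario.

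| Truth | Friedman rejects | Mixed ANOVA term that addresses it |
|---|---|---|
| Group effect only | 4.9% | 100% (group) |
| Opposite priming effects across groups | 1.3% | 100% (group × priming) |
| Priming response in healthy controls only | 44.7% | 95.8% (group × priming) |
| Same priming response in all groups | 100% | 5.2% (group × priming) |

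The last two rows matter most. A significant Friedman result can arise when only controls respond or when everyone responds, and it cannot tell the two apart.

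**4. How often the fallback would be entered.** The protocol does not say whether K-S is run per cell or on pooled data, with or without the Lilliefors correction, or how many rejections count. Assume normalized MEP is lognormal, n = 15 per cell, and 3 groups × 3 primings × 3 post-baseline times = 27 cells treated as independent. The chance of at least one rejection is 1 − (1 − p)^27.

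| Log-SD | Lilliefors p per cell | Any of 27 | Uncorrected p per cell | Any of 27 |
|---|---|---|---|---|
| 0.3 | 12.6% | 97% | 0.1% | 3% |
| 0.5 | 26.4% | >99% | 0.7–1.0% | 17–24% |
| 0.7 | 43% | >99% | 2.8% | 54% |

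Examples: 1 − 0.874^27 = 0.97; 1 − 0.972^27 = 0.54. The range in the middle uncorrected row is simulation error between runs. With exactly normal data and a true 5% test, 1 − 0.95^27 = 0.75. The spread is therefore about 3% to nearly 100%, depending on choices that the text does not make.

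**5. The plan's own figure.** Sample size (2.3) gives 15 per group from f = 0.3, 80% power, 5% alpha and 20% loss for a three-way repeated measures ANOVA. The number of measurements and the correlation are not stated, so the figure cannot be uniquely reproduced. One variant gives it exactly: the within-between interaction with 3 measurements and correlation 0.3 needs 12 per group, and 12 / 0.8 = 15. Nothing here shows that 15 is wrong. The power statement belongs to the ANOVA and does not carry over to Friedman.

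**The case against.** **Other planned comparisons survive.** This stands. A reader might infer that the switch leaves the whole primary question unanswerable, the first hypothesis untestable, and MCS and UWS uncompared. The protocol does not support that. Statistical analysis (2.11) also asks whether cathodal tDCS plus iTBS beats iTBS alone; this is within-subject, and Friedman across priming conditions at a fixed time can address it. The MCS-versus-UWS comparison of preservation is mentioned separately and not tied to the normality result, although its test is not named. The second part of the first hypothesis, a correlation with level of consciousness, has its own Pearson analysis.

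**The fallback may rarely be used.** Partly stands. A reader might take its use as near certain because a positive ratio can be skewed. The protocol gives no distribution for normalized MEP and no rule for applying K-S, and the uncorrected version rejects seldom at n = 15. The defect does not depend on the frequency: whenever the rule fires, the replacement fails.

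**Friedman could be run within each group.** This does not repair it. Significance in one group and not in another is not a test of the difference between them. The named follow-up analyses are within-group too, parametric, and conditional on a significant ANOVA.

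**A separate SAP would settle it.** That would answer an omission. Here a specific, unsuitable test is written into the protocol.

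**Conclusion.** The point holds in a limited form. If K-S rejects, the healthy-versus-DoC comparison that the protocol names as its primary focus, and every interaction with group, are left without a valid named test. That follows from the structure of Friedman's test and rests on no assumption. The size of the loss is complete for those effects: rejection stays at or below the nominal 5% for a pure group effect and for an opposite-direction interaction, where a test retaining group reached 100% under the simulated SDs and shifts.

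The probability of reaching that state is open. It ranges from about 3% to nearly 100% across the K-S variants and the assumed log-SD of 0.3 to 0.7, with independent cells and an any-of-27 rule. No single trigger rate should be quoted. The within-subject cathodal-versus-sham question, the MCS-versus-UWS comparison and the Pearson correlation are not removed by the switch. The rule should be corrected before any data are analysed, because it governs the primary comparison and is cheap to change.

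**What to change.** Delete the K-S/Friedman switch and pre-specify one analysis that keeps both the group factor and the session-baseline adjustment:

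- **Outcome.** Log(MEP / session baseline), or log(MEP) with log session baseline as a covariate. Log(MEP) at the post-baseline times with no baseline term would not do, because it discards the adjustment that the protocol calls for.
- **Model.** Group × priming × time over INTER, POST-1 and POST-2, as a linear mixed model with participant and session-within-participant effects. The planned three-way ANOVA on the log ratio would also repair the defect. State the healthy-versus-DoC contrast explicitly. PRE is left out as a time level because after normalization it equals 1 for everyone.
- **Checks.** Examine model residuals, not the raw data, and do not let a preliminary test choose the analysis.
- **Sensitivity, if wanted.** A rank-based factorial method that retains group and its interactions, or permutation. For a group × priming question, for example, form each participant's cathodal-minus-sham difference in log ratio and permute the group labels.

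The cost is a few lines of analysis wording, with the same data, participants and software. The one consequence for reporting is that effects are given as ratios of geometric means.

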Given the negative feedback mechanism of homeostatic plasticity, we can propose a priming-test preconditioning TMS tool that is more effective than the current stimulation alone. Initially, subjects will receive inhibitory priming to trigger their homeostasis response, followed by an excitatory test. As a result of the preceding inhibitory treatment, the neural network near the subject’s target area will more readily generate an excitatory response, leading to a more significant neural network activity during the excitatory test compared to the excitatory stimulus alone. Homeostatic plasticity plays a critical role in maintaining neural stability; thus, its impairment could limit the efficacy of NIN interventions. Research on myasthenia gravis (18), dystonia (19–21), Parkinson’s disease (22), Alzheimer’s disease (23), depression (24) and other psychiatric disorders (25) have highlighted deficiencies in homeostatic plasticity among patients, raising concerns about its preservation in DoC patients.

Therefore, prior to administering the combined stimulation to DoC patients, it is crucial to investigate the preservation of homeostatic plasticity in these individuals. This study is guided by two hypotheses: firstly, that DoC patients exhibit impaired homeostatic plasticity, with the degree of impairment correlated with their level of consciousness; and secondly, that patients who retain homeostatic plasticity may have a more favorable prognosis. To explore the retention of homeostatic plasticity in DoC patients, this study will employ two NIN technologies, tDCS and TMS, as assessment tools.

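### The plan does not require a significant group interaction before within-group MEP results are read as preserved or impaired plasticity

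*Protocol article*

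**What the plan says.** All references are to the protocol article.

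- **Hypothesis (Introduction).** The first hypothesis is "firstly, that DoC patients exhibit impaired homeostatic plasticity, with the degree of impairment correlated with their level of consciousness".
- **Primary aim (section 2.11).** It is stated that "the primary focus of this study will be to analyze the trend of MEP changes over time in different priming types, comparing healthy individuals with" patients with DoC. The same paragraph says that the ANOVA on baseline-normalized MEP will also serve "to determine whether the combination of cathodal tDCS and iTBS is superior to iTBS alone".
- **Main model (section 2.11).** "If the data meets the criteria for a normal distribution, a three-way repeated measures ANOVA will then be carried out". The three factors are not listed; group, priming and time are the evident reading.
- **Fallback (section 2.11).** "However, if the data does not adhere to a normal distribution, Friedman’s ANOVA will be utilized instead".
- **Follow-up (section 2.11).** "Following a significant outcome from the ANOVA, two-way ANOVAs will be conducted within each group to explore temporal changes in mean MEP amplitude".
- **Definition (section 2.11).** "A preserved homeostatic plasticity response is defined as a significant modulation of MEP amplitude following the priming-test protocol", in line with the sliding threshold theory. Preservation is then compared between MCS and UWS and between good and poor prognosis. Healthy controls are not in that list.

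**The concern.** The hypothesis is comparative: plasticity in DoC is worse than in healthy people. The steps that lead to the label are not. The gate is a significant outcome of a model with seven effects, and none of them is singled out. The analyses behind the gate are run separately in each group. Preserved means significant, so the natural complement, impaired, is not significant. A reader who follows these steps can find a significant response in healthy controls, none in MCS or UWS, and conclude impairment. A difference in significance is not a test of a difference, and groups with the same true response will often differ in significance at this sample size.

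The label carries weight. The Discussion raises the possibility that impaired plasticity marks an irreversible condition, and it expects the result to affect how these patients are managed.

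**Working it through.** **Inputs from the article.** Three groups of 15 (section 2.2); 20% data loss, so 15 × 0.8 = 12 evaluable per group (section 2.3); three priming conditions and four MEP time points (section 2.4), of which three are informative after division by baseline; significance at 0.05 (section 2.11).

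**Inputs that are assumptions.** The article gives no power for the within-group tests. Call it w, equal in all groups, with identical true effects and independent groups.

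**Step 1: how often the groups disagree by chance.**

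- Healthy controls significant: w.
- At least one of MCS and UWS not significant: 1 − w².
- Both together: w(1 − w²).
 - w = 0.5: 0.5 × 0.75 = 0.375.
 - w = 0.8: 0.8 × 0.36 = 0.288.
 - Maximum at w = 0.577: 0.385.
- Stricter pattern, healthy significant and both patient groups not: w(1 − w)².
 - w = 0.5: 0.5 × 0.25 = 0.125.
 - w = 0.8: 0.8 × 0.04 = 0.032.

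**Step 2: whether the gate prevents this.** This was checked by simulating a 3-group × 3-priming × time mixed ANOVA with identical true effects in all groups. There were 10,000 runs per setting, 12 or 15 per group, 3 or 4 time points, subject SD = residual SD = 1, and sphericity. Preserved was read from the within-group priming × time test, whose power ran from about 0.12 to 0.79 across settings.

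| | Gate: any effect significant | Gate: group × priming × time significant |
|---|---|---|
| Gate opens | 87% to 100% | about 5% |
| Healthy significant, at least one DoC group not | 12% to 38% | 1.3% to 2.4% |
| Healthy significant, both DoC groups not | 4% to 15% | 0.1% to 1.1% |

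When a shared priming or time effect exists, a gate that accepts any effect is nearly always open, so it gives almost no protection. A gate on the interaction removes most of the problem.

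**Step 3: the non-normal branch.** Friedman's test ranks repeated measurements on one factor within subjects. It has no between-group term. If normality is rejected, the named procedure offers no comparison of DoC with healthy controls.

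**Step 4: the superiority question.** Whether cathodal priming plus iTBS beats iTBS alone is one directional contrast, cathodal minus sham. An omnibus F test over three priming levels does not give its direction or its size.

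**The case against.** Several points count against a stronger reading.

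- **The gate.** A reader might infer that any significant effect opens the follow-ups. The text does not say that; it leaves the effect unnamed. Read with the primary aim, the intended outcome may well be the group × priming × time interaction.
- **The group test.** A reader might infer that DoC is never tested against healthy controls. In the normal branch that is not supported. The primary aim and the within-group follow-ups imply that group is a factor, and the three-way ANOVA then computes the interaction before any follow-up. Only the Friedman branch lacks a group test.
- **The rule.** No sentence says that impairment is declared from within-group p-values alone, and the follow-ups are described as exploratory. The definition of preserved also does not say whether it applies to a group or to a patient. What stands is that neither reading of it refers to controls, and no sentence ties impairment to the interaction.
- **The superiority question.** The comparison of cathodal with sham is planned, at the individual level, although no test is named for it. It would be wrong to call it absent.
- **Condensed article.** Contrasts are often left to an analysis plan. Here, however, the article itself fixes the gate, the follow-ups, the definition and the fallback, and together these permit an invalid inference.

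**Conclusion.** The point holds in a limited form. The plan does not tie the conclusion of impairment to a significant group interaction, and its fallback has no group term. With identical true effects, the misleading pattern of healthy significant and at least one patient group not has probability 37.5% at w = 0.5 and 28.8% at w = 0.8. With the interaction as gate it falls to about 1–2%. These sizes rest on the assumed w and on the simulation's variances and sphericity, none of which is in the article. The contrast between the two gates matters more than any single figure.

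Two larger sizes are tempting and should not be used. The chance of at least one false positive among seven independent effects, 1 − 0.95⁷ = 30.2%, requires all seven to be null, and a true time effect after iTBS is not a false positive. Counting every disagreement between groups gives 2w(1 − w) = 50% for two groups and 1 − w³ − (1 − w)³ = 75% for three at w = 0.5. Those figures include patterns with patients significant and healthy controls not, which nobody would read as impairment in DoC.

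**What to change.** 1. Name the healthy-versus-DoC interaction as the test of impairment: either group × priming × time, or the group difference in the cathodal-minus-sham change after iTBS. The contrast has the advantage of a direction and an interpretable size.
2. State that non-significance within DoC alone is not evidence of impairment.
3. Report the cathodal-minus-sham effect with a 95% CI in every group, whatever the interaction shows, as the answer to the superiority question. Opening these estimates only after a significant interaction would block that question exactly when DoC patients respond like healthy controls.
4. Replace Friedman's test with a fallback that keeps the group term, for example a rank or permutation comparison between groups of each participant's cathodal-minus-sham change.

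The cost is small: wording in section 2.11, with the other ANOVA effects and the within-group p-values becoming descriptive. Section 2.3 does not say which effect the sample size was calculated for, so the power or expected precision for the named test should be stated alongside it.

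### The plasticity–prognosis analysis is unadjusted for baseline consciousness and leaves the form of its variables open, so it cannot show prognostic value beyond MCS/UWS status

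*Protocol article*

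**What the plan says.** The Introduction sets two hypotheses. The first is that homeostatic plasticity is impaired in DoC, "with the degree of impairment correlated with their level of consciousness". The second is that "patients who retain homeostatic plasticity may have a more favorable prognosis".

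Section 2.11 defines each of the three quantities as a category:

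- Consciousness: "patients will be classified into the MCS or UWS group based on the best result from five baseline CRS-R assessments".
- Prognosis: patients gaining more than 11 Rasch units form the good group, and "others will be placed in the poor prognosis group". Follow-up is at 3, 6 and 12 months.
- Retention: "A preserved homeostatic plasticity response is defined as a significant modulation of MEP amplitude following the priming-test protocol".

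Preservation is then compared between MCS and UWS and between the prognosis groups. In addition, "Pearson correlation will be used to examine the relationship between homeostatic plasticity retention, consciousness, and prognosis". No covariate or partial correlation is named for either analysis, and no continuous retention index is defined.

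**The concern.** The two hypotheses are not separable by a bivariate analysis. If plasticity tracks level of consciousness, as the first hypothesis says, and level of consciousness is related to recovery, then retention and prognosis will be associated even when plasticity carries no information beyond MCS/UWS status. The Discussion (section 3) supports both links: it says that homeostatic plasticity reflects levels of consciousness, and it ties MCS to a window for recovery.

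This matters because of the use foreseen for the result. The Discussion suggests that impaired plasticity might in some cases signal an irreversible condition, and that retention status will weigh on clinical management. MCS/UWS status is already known from the baseline CRS-R, so that use needs evidence that plasticity adds to it.

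A second, conditional matter is information loss. Serial CRS-R scores and MEP ratios are collected. If only the defined categories enter the correlation, the Pearson coefficient is a phi coefficient and much of the power in 30 patients is given up.

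**Working it through.** **The plan's own figure.** There is none for this analysis. The 15 per group in section 2.3 belongs to the repeated-measures ANOVA. It can be reached, for example, with three groups, three measurements and an assumed correlation of 0.3 among them: 12 per group, and 12/0.8 = 15 after 20% loss. It says nothing about the correlation.

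**Inputs from the protocol.** 15 MCS and 15 UWS patients (section 2.2), so n = 30, or 30 × 0.8 = 24 after the 20% loss in section 2.3. Alpha is 0.05 (section 2.11), taken as two-sided.

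**Inputs assumed.** The documents give no rates of retention or good prognosis by group. A range is shown.

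**Step 1: association induced by baseline status alone.** Let retention and prognosis be independent within MCS and within UWS, with equal group sizes. With retention rates a (MCS) and b (UWS), good-prognosis rates c and d, and overall means p and q,

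phi = [(a − b)(c − d)/4] / √[p(1 − p) q(1 − q)].

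Example: retention 80/20%, good prognosis 60/10%. The numerator is 0.60 × 0.50/4 = 0.075. The denominator is √(0.5 × 0.5 × 0.35 × 0.65) = 0.2385. So phi = 0.31.

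Rejection by the ordinary Pearson t-test at n = 30 (simulation, 40,000 runs per row):

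| Retention MCS/UWS | Good prognosis MCS/UWS | phi | Unadjusted rejection |
|---|---|---|---|
| no difference | any | 0 | 5.1% |
| 60/40% | 50/20% | 0.06 | 6.2% |
| 70/30% | 50/20% | 0.13 | 10.6% |
| 80/20% | 50/20% | 0.19 | 17.9% |
| 70/30% | 60/10% | 0.21 | 21.5% |
| 80/20% | 60/10% | 0.31 | 41.8% |
| 80/20% | 70/10% | 0.37 | 53.9% |

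A partial correlation given MCS/UWS rejects in 4.2–5.1% in every scenario. A fresh simulation of the n = 30 rows agreed to within about 1 percentage point.

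**Step 2: cost of dichotomising, if it is done.** For a bivariate normal pair split at both medians, phi = (2/π) arcsin(r). At r = 0.4 this is 0.637 × 0.412 = 0.26, and (0.26/0.4)² keeps about 43% of the effective sample size. Simulated power at a true r of 0.4:

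| Variables | n = 30 | n = 24 |
|---|---|---|
| Both continuous | 61% | 50% |
| Both split 50/50 | 28.5% | 26% |
| 50% preserved, 30% good prognosis | 26% | 23% |
| 50% preserved, 20% good prognosis | 22% | 18% |

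Dichotomising prognosis only gives 33–41% at n = 30.

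**Step 3: what is detectable at best.** With continuous data, r for 80% power = tanh[(1.960 + 0.842)/√(n − 3)]. For n = 30 this is tanh(2.802/5.196) = 0.49. For n = 24 it is tanh(2.802/4.583) = 0.55.

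**The case against.** Several points on the other side stand.

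- **Which form is correlated.** A reader might infer that the dichotomised variables are certainly what is correlated. Section 2.11 never says so. The Introduction speaks of a degree of impairment, normalised MEP is a ratio, the CRS-R score is the secondary outcome, and the categorical comparisons are listed separately. A continuous reading is plausible, so the loss in Step 2 is conditional.
- **Confounder or mediator.** Section 2.11 also says that homeostatic plasticity may influence consciousness and prognosis. On that view baseline consciousness lies on the pathway, and adjustment would remove part of the association of interest. Adjustment alone is therefore not the single right answer.
- **Association only.** The second hypothesis, as worded, does not claim independence from baseline. In the Step 1 scenarios the marginal association is real, so rejecting zero correlation is an error only for a claim of added value.
- **Change score.** Good prognosis is a gain from baseline, so its relation to baseline may be weak or may run either way.
- **A single false-positive figure.** A reader might assume correlations of 0.5 (retention–baseline) and 0.5–0.6 (baseline–prognosis), get an induced r of 0.25–0.30, and quote 26–36% as the false-positive rate. The documents give none of these inputs. The figure also presumes undiminished continuous correlations: with both variables split (factor about 0.64), r is 0.16–0.19 and the same Fisher-z formula gives about 13–17%.
- **Scope.** A condensed article may leave coding and covariates to a fuller document, and this analysis supports the MEP ANOVA rather than replacing it.

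The reply to the last point is limited. The article does fix the test and the categories, and the group comparison that accompanies the correlation shares its lack of adjustment. Nothing in the document separates the prognosis hypothesis from baseline consciousness.

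**Conclusion.** The point holds in a limited form. As written, a plasticity–prognosis association could partly or wholly restate baseline MCS/UWS status, and would not by itself support the prognostic use described in the Discussion. How far this goes cannot be told from the documents. Unadjusted rejection with no within-group link runs from the nominal level to about 54%, wholly according to the assumed rates. The protocol does not establish that baseline consciousness is a common cause, nor that binary variables enter the correlation. If they do, power at a true r of 0.4 and n = 30 drops from about 61% to 22–29%. Even the best continuous analysis has 80% power only for correlations of about 0.49 to 0.55, so it is exploratory on any reading.

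**What to change.** In section 2.11:

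1. Define one continuous plasticity index from the normalised MEP data, for example the cathodal minus sham difference in log MEP ratio, and state that this is what is related to consciousness and prognosis.
2. In the patients, regress the CRS-R Rasch score at one named follow-up time on this index, with the baseline CRS-R Rasch score as covariate. A partial rank correlation would also serve.
3. Report the adjusted estimate with its 95% confidence interval beside the unadjusted one, and say that baseline consciousness may be a confounder or a mediator.
4. Keep the good/poor split as descriptive, and label the analysis exploratory at 24–30 patients.

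The data are already planned: baseline CRS-R (section 2.2), follow-up CRS-R (section 2.8) and normalised MEP (section 2.11). The cost is one degree of freedom for the covariate, some rewording and a little more analysis work.
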